### Statistical Analysis

Data collected within the pilot study will be analyzed using an exploratory approach. Descriptive analysis will give information on the cumulative trends of exposures to different PM fractions, their metal content and other airborne chemicals. Direct-reading fine and ultrafine particle exposure measurement data (from DISCmini and Grimm, Table 1) will be analyzed along with data from the activity logbooks, using time series analytical technics such as Bayesian spline analysis to get insights on the exposure sources and determinants.

Repeated data will be analyzed using mixed linear models and interval regression models for the censured data (below LOD/LOQ). Air and biomarker concentrations will be compared between occupations, using daily, pre- and post-shift log-transformed mean values with and without adjustment for variables collected through the standardized questionnaire (e.g., age, average home-to-work commute time, anti-oxidant diet, non-occupational exposure to PM). Correlation between external and internal exposure (based on urine and EBC biomarkers of exposure), internal exposure and early effect biomarkers, and the latter with FEV1/FVC will be tested, using post-shift to pre-shift values ratios for each biomarker. Analysis will be conducted applying different lag-times on the exposure estimates (e.g., 6 h, 14 h, and 24 h) to explore the temporal variation in biomarker levels. The most informative biomarkers (i.e., correlated both with exposure and particularly with FEV1/FVC ratio) will be selected for the field study.

In the field study, the central research hypothesis is that a panel of oxidative stress biomarkers measured in non-invasive samples, including OPEA will be more efficient for COPD diagnosis than single biomarker analysis. This hypothesis will be tested using generalized linear models. Besides, additional associations between dependent variables and explanatory variables will be examined, as shown in Fig. 3. Data management and statistical analyses will be performed using Stata, version 16, software.

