***Biomarkers of exposure***		
Transition metals (Fe, Cu, Zn, Mn, Co, Cr, Ni, Mo, Ti,V), Ba, Sb, S, Si, Al, Pb mass concentration	EBC	ICP-MS
Nanoparticles number concentration and mean hydrodynamic diameter	EBC	Nanoparticle Tracking Analyser (Malvern)
Transition metals (Fe, Cu, Zn, Mn, Co, Cr, Ni, Mo, Ti,V), Ba, Sb, Si, Al, Pb mass concentration	Urine	ICP-MS
PAH metabolites (1-hydroxypyrene)	Urine	HPLC-Fluo

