***Biomarkers of effect***		
OPEA	Alveolar and bronchial part of the exhaled air	OPEA analyser + FOX colorimetric test (6 min including sampling)
Fractional Exhaled Nitric Oxide (eosinophilic inflammation)	Exhaled air	Direct-reading instrument
8-isoprostane, malondialdehyde (lipid peroxidation)	EBC	HPLC-MS/MS
8-hydroxy-2’deoxyguanosine (DNA-oxdation)	EBC	HPLC-MS/MS
NO2^−^, NO3^−^ and formate ion (nitrosant stress)	EBC	Ion-chromatography
Acetate, pyruvate, lactate, butyrate, propionate (cell metabolism)	EBC	Ion-chromatography
Malondialdehyde	Urine	HPLC-MS/MS
8-isoprostane and 8-hydroxy-2’deoxyguanosine	Urine	UPLC-MSMS
Creatinine	Urine	LC-MS/MS
Micronuclei (genotoxicity)	Buccal cells	Buccal micronuclei cytome assay

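### Pilot correlations between exposure and effect markers from the same breath-condensate sample can arise from a pre-to-post change in dilution, and they count towards marker selection

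*Protocol article*

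**What the plan says.** The Statistical Analysis section calls the pilot analysis exploratory and then names a chain of correlations: external with internal exposure, internal exposure with early effect markers, and effect markers with lung function. Internal exposure is defined there as "internal exposure (based on urine and EBC biomarkers of exposure". The form of the variables is fixed in the same sentence: "internal exposure and early effect biomarkers, and the latter with FEV1/FVC will be tested, using post-shift to pre-shift values ratios for each biomarker".

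Table 2 gives the matrices. Among the exposure markers, EBC carries sixteen elements by ICP-MS and "Nanoparticles number concentration and mean hydrodynamic diameter"; urine carries metals and "PAH metabolites (1-hydroxypyrene". Among the effect markers, EBC carries "8-isoprostane, malondialdehyde (lipid peroxidation", 8-OHdG and eight anions; urine carries MDA, 8-isoprostane and 8-OHdG. Creatinine is listed for urine. No dilution measure is listed for EBC. OPEA and FeNO are measured in exhaled air and micronuclei in buccal cells.

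The results feed a decision: "The most informative biomarkers (i.e., correlated both with exposure and particularly with FEV1/FVC ratio) will be selected for the field study". The section Exposure and Health Outcome Measures then restricts the field study to the markers chosen in the pilot.

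**The concern.** The concentration of any analyte in a condensate sample depends on how dilute that sample is. If the post-shift sample is more concentrated than the pre-shift one, the post/pre ratio of every concentration from it rises together, whether or not the analytes are biologically linked. Taking a ratio cancels what is constant within a worker and leaves this change in place. A correlation of zero is then the right reference only if dilution does not change over the shift.

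The comparison between candidates is also uneven. An EBC effect marker can gain an apparent exposure link from shared dilution. OPEA and FeNO cannot, because no exposure marker is listed in exhaled air. The listed correlations connect effect markers to exposure only through internal exposure, so the artefact sits in the link that supplies their exposure evidence.

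**Working it through.** **Size of the analysis.** The Discussion states twenty urine and EBC measurements per participant. Two weeks × 5 shifts per week (assumed) × 2 samples per day = 20, which reproduces it. That is 10 post/pre ratios per worker, and 9 workers × 10 = 90 ratios.

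**Pairs concerned.** From Table 2, EBC exposure concentrations are 16 elements + nanoparticle number = 17. EBC effect concentrations are 8-isoprostane, MDA, 8-OHdG and 8 anions = 11. That gives 17 × 11 = 187 possible same-sample pairs. Mean hydrodynamic diameter is a size, not a concentration, and is left out.

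**Mechanism.** For markers x and y from one sample, write the log post/pre ratios as

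- Lx = mx + d
- Ly = my + d

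where mx and my are the true changes and d is the change in log dilution, common to both. With mx and my independent of each other and of d, Cov(Lx, Ly) = Var(d). If d accounts for shares sx and sy of the two variances, the induced correlation is ρ = √(sx·sy), which equals s when the shares are equal.

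**False-positive rate.** Assumptions not in the article: two-sided 5% level, ratios centred within worker, equal shares. Centring uses 9 means and leaves 80 degrees of freedom for the correlation, equivalent to n = 82. By Fisher's z, the test statistic is shifted by atanh(s) × √(82 − 3) = atanh(s) × 8.888, and the rejection rate is Φ(shift − 1.96) + Φ(−shift − 1.96).

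| Dilution share s | Shift | False positives |
|---|---|---|
| 0 | 0 | 5.0% |
| 0.05 | 0.445 | 7.3% |
| 0.10 | 0.892 | 14.5% |
| 0.20 | 1.802 | 43.7% |
| 0.30 | 2.751 | 78.6% |

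Simulation of 9 workers × 10 ratios agrees to within about one percentage point. With independent dilutions, as assumed for one marker in EBC and the other in urine, the simulated rate stays at 5% even at s = 0.30.

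**Unequal shares.** If dilution explains 0.30 of one marker's variance and 0.05 of the other's, ρ = √(0.30 × 0.05) = 0.122 and the rate is about 19%. The bias shrinks quickly when either marker is little affected.

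**The case against.** The case on the other side has five parts.

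- **Silence about normalisation.** The article does not say that the ratios use uncorrected values. Normalisation may be set out in a fuller document, and listing creatinine suggests correction is intended for urine. This stands for urine. It is weaker for EBC, where Table 2 names nothing to correct with.
- **Exploratory status.** No level, threshold or formal null hypothesis is given. A reader might infer that a confirmatory test has an invalid error rate; the article does not support that, and the percentages above only gauge the bias. But the correlations still serve a stated selection rule, so the exploratory label does not remove the consequence.
- **A joint rule.** A marker must also correlate with FEV1/FVC, which carries the greater weight and shares no sample dilution with any biomarker. A reader might infer that the field panel will be chosen wrongly. That goes too far: a spurious exposure correlation cannot select a marker alone, and the diagnostic hypothesis is tested afresh in about 300 workers.
- **Unknown size.** The range runs from trivial to large, and one device with a fixed 20-minute collection may limit dilution changes. This is fair; the article gives no figure either way.
- **Other exposure evidence.** The plan to apply lag times to exposure estimates could be read as covering effect markers against air measurements. If so, it is not spelled out, and the list of correlations does not include that link.

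**Conclusion.** The point holds in a limited form. For exposure and effect concentrations from the same EBC sample, the planned post/pre ratio leaves a shared dilution change in both variables, so a correlation can appear without any exposure-effect link. Over dilution shares of 0.05 to 0.30, a nominal 5% false-positive rate becomes about 7% to 79%. This rests on assumed shares, a 5% within-worker test, 90 ratios, and EBC assays that draw on one collection per visit.

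The reach is narrow. It touches only the exposure part of the selection rule. It does not touch the FEV1/FVC correlations, the external-internal correlations, cross-matrix pairs with independent dilution, OPEA, FeNO, micronuclei or mean hydrodynamic diameter. A reader might extend it equally to urine. The article does not support that, because creatinine is measured and its use may be described elsewhere. The issue is worth correcting because it favours EBC markers over exhaled-air markers and the means to check it are already being collected.

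**What to change.** In the Statistical Analysis section:

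1. Add direct correlations between each effect marker and personal air exposure.
2. State that a same-sample EBC correlation counts as correlated with exposure only when personal air or urinary exposure supports it, and is otherwise reported as descriptive.
3. For pairs within urine, state how creatinine is used, for example by entering its log post/pre ratio as a covariate. Dividing both markers by creatinine puts creatinine's own noise into both. In a simulation with a dilution share of 0.30 and noise making up 20% or 40% of creatinine's variance, false positives were 11.6% or 25.4% with the covariate and 14.3% or 51.7% with division. Neither is a complete cure.

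No new measurement is needed. The main cost is that a few true same-sample EBC links may go uncredited. The article says that some statistical analysis has begun, so the change should be dated, with a note of whether any of these correlations had been seen.

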The constraints of our pilot study protocol entailed a very intensive field data collection from no more than nine participants, with one physician, one nurse, two PhD students, and a support team of five technicians present in the companies over six weeks. Given the diversity of exposure metrics and measurements and devices available it was hardly possible to include more participants. This drawback of the very complete exposure assessment in the pilot study, will be compensated with a large probabilistic sample in the field study. The latter is expected to have 90% statistical power to discriminate COPD cases from controls based on a quite small OPEA difference. On the other hand, a possible lack of power induced by the relatively small number of workers included in the pilot study will be compensated for by the exposure variance when including both highly exposed and less exposed workers, such as locomotive operators and station agents, respectively. It is noteworthy that the repeated measure design (twenty measurements per participant for urine and EBC) will contribute to increase the power of detecting short-term effects.

Bacterial contamination and endotoxin measurements were not included in the protocol due to limited resources, but also because these exposures do not raise any particular concern at the company. However, the COVID-19 pandemic has strongly affected the working conditions of subway professionals and possibly the respiratory health of those who have contracted this disease. If the pandemic continues, then this situation is likely to be an issue for a timely start and progress with the field study. To guaranty the participant and staff safety, the planning and logistics of worker medical checks should be revised. This may delay the sample and data collection process, but also decrease the participation rate. Indeed, additional time, equipment and human resources will make the field study more expensive.

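### The pilot selects biomarkers on post-/pre-shift ratios and then adds 6, 14 and 24 h exposure lags without fixing the outcome scale; on the ratio, responses delayed about 14–24 h would look inverse or null

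*Protocol article*

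**What the plan says.** All of this is in the Statistical Analysis section of the protocol article unless stated otherwise.

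- Three links are to be tested by correlation: external with internal exposure, internal exposure with early effect biomarkers, and effect biomarkers with FEV1/FVC. The scale is given as "using post-shift to pre-shift values ratios for each biomarker".
- The next sentence plans analyses "applying different lag-times on the exposure estimates (e.g., 6 h, 14 h, and 24 h) to explore the temporal variation in biomarker levels".
- The sentence after that gives the selection rule: "The most informative biomarkers (i.e., correlated both with exposure and particularly with FEV1/FVC ratio) will be selected for the field study".
- The same paragraph also names mixed linear models, and interval regression for values below the detection or quantification limit. It compares occupations "using daily, pre- and post-shift log-transformed mean values". Ratios are therefore not the only scale in the pilot.
- Under Exposure and Health Outcome Measures, samples are taken before and after each shift. In the field study the selected biomarkers are measured once per worker.
- Under Aims and Design of the Study, aim 2 is to set the sampling plan by biomarker half-life and aim 4 is to select the biomarkers for the field study.
- The Discussion says that "the repeated measure design (twenty measurements per participant for urine and EBC) will contribute to increase the power" to detect short-term effects.

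**The concern.** A post-/pre-shift ratio isolates what changed during one shift. It suits a marker that responds within that shift. For a marker that responds later, the previous day's exposure raises the next pre-shift value, which is the denominator. If the rise has faded by the post-shift sample, higher exposure gives a lower ratio. If the rise is equally present in both samples, it cancels.

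Two of the three example lags, 14 and 24 h, lie where this happens. What is at stake is a decision: the correlations choose the markers for the field study, and the pilot is meant to find out when to sample. A delayed marker could be rejected or assigned the wrong timing. The field study will then have a single level per worker, so selection on ratios also rests on a scale that the field study cannot reproduce.

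**Working it through.** **1. The plan's own count.** Two samples a day × 5 working days × 2 weeks = 20 per participant, which matches the Discussion. Five working days a week is an assumption; it is the value that gives 20.

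**2. Algebra.** Let the previous day's exposure raise the log pre-shift level by b per unit, and the log post-shift level of that same later day by c·b, where c is the carry-over. The slope of log(post/pre) on prior-day exposure is c·b − b = b(c − 1). For an illustrative b = 0.20:

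- c = 0: −0.20
- c = 0.5: −0.10
- c = 1: 0
- c > 1 (response still rising): positive, the right sign

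The pre-shift level itself gives +0.20 in each case.

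**3. Where one shift's exposure falls.** The shift length of 6–8 h is from the Abstract. Sampling 0.5 h before and 0.5 h after the shift is an assumption, consistent with workers being received an hour beforehand. The time from exposure to sample is then:

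| Shift | Same-day post | Next pre | Next post |
|---|---|---|---|
| 6 h | 0.5–6.5 h | 17.5–23.5 h | 24.5–30.5 h |
| 8 h | 0.5–8.5 h | 15.5–23.5 h | 24.5–32.5 h |

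**4. Weight of the response in each sample.** Assume a bell-shaped response with its peak at m hours and SD s hours. The weight in a window from l to u is Φ((u − m)/s) − Φ((l − m)/s). For an 8 h shift, m = 14 and s = 4:

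- next pre: Φ(2.375) − Φ(0.375) = 0.345
- next post: Φ(4.625) − Φ(2.625) = 0.004
- prior-day coefficient on the log ratio: 0.004 − 0.345 = −0.341

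The same calculation at other peaks (8 h shift, s = 4):

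| Peak | Same-day post | Next pre | Next post | Prior-day coefficient on log ratio |
|---|---|---|---|---|
| 6 h | 0.649 | 0.009 | 0.000 | −0.009 |
| 14 h | 0.084 | 0.345 | 0.004 | −0.341 |
| 18 h | 0.009 | 0.649 | 0.052 | −0.597 |
| 24 h | 0.000 | 0.434 | 0.434 | 0.000 |
| 28 h | 0.000 | 0.129 | 0.679 | +0.550 |

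Over both shift lengths and s = 2 or 4, the prior-day coefficient runs from −0.04 to −0.89 for peaks of 14 and 18 h. It is 0.00 at 24 h and +0.42 to +0.94 at 28 h.

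**5. Immediate response with exponential decay.** For half-lives of 3 to 72 h, the same-day coefficient on the ratio is +0.41 to +0.96, so the acute effect is seen. The prior-day coefficient is −0.01 to −0.13, although prior-day exposure raises the pre-shift level by 0.013 to 0.829. The ratio thus hides the persistence that aim 2 needs to know about.

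**6. Simulation.** 2000 pilots of 9 workers × 10 days, 8 h shift, s = 4. Assumed values: exposure SD 0.5, effect 2, between-worker SD 0.8, residual SD 0.4, all on log scales. The first day of each week has no measured prior-day exposure and is left out of the lagged correlations. Mean correlations (levels are taken within worker):

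| Peak | Ratio, prior day | Pre level, prior day | Post level, prior day | Ratio, same day |
|---|---|---|---|---|
| 6 h | −0.02 | +0.02 | −0.09 | +0.75 |
| 14 h | −0.51 | +0.65 | −0.01 | +0.14 |
| 18 h | −0.72 | +0.85 | +0.13 | +0.01 |
| 24 h | 0.00 | +0.73 | +0.73 | 0.00 |
| 28 h | +0.69 | +0.31 | +0.86 | 0.00 |

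These figures concern the link from measured exposure to a biomarker. The link with FEV1/FVC was not simulated.

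**The case against.** The strongest reply is that the conflict is inferred. The ratio belongs to the correlation sentence. The lag sentence follows it and speaks of biomarker levels, so the authors may have meant to use levels there. The 14 h example is also close to the shortest gap in step 3 between the end of a shift and the next pre-shift sample (15.5 h), which would suit an analysis of the pre-shift level. The pilot is declared exploratory, models for repeated data are named, and an article leaves model detail to the full plan. For same-shift effects the ratio is a sound choice, because it removes stable differences between workers.

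Most of this stands, and it is why the point is conditional. It does not remove the point. The ratio is fixed for every biomarker in the correlations, selection follows directly from correlation, and the only analysis expressly placed on pre- and post-shift levels is the comparison of occupations, which is not the stated selection criterion. An exploratory label does not help when the output is a decision on which markers go forward.

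Three stronger readings are tempting, and the documents do not support them:

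- *Delayed responses always show the wrong sign.* They do not. The sign reverses at about 14–18 h, vanishes at about 24 h and is right at about 28 h.
- *Half the data are lost.* Each ratio uses both samples. Only the correlation step has 10 values per worker instead of 20 (90 instead of 180 over nine workers). The Discussion's count of measurements is true and does not promise 20 outcomes in every test.
- *The method for values below the detection limit is defeated.* Interval regression is attached to repeated data in general. A ratio with one censored value is still a usable one-sided interval; only a pair with both values censored carries no information. If 30% of values were below the limit, with a pre/post correlation of 0.3–0.8 (both assumed), 13–21% of pairs would be of that kind.

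**Conclusion.** The point holds in conditional form. The outcome scale of the lagged analyses is not clearly stated, and the scale stated for the selecting correlations is the wrong one for delayed responses. If the ratio is used with lagged exposure, a true positive response peaking at 14 h gives a correlation of −0.51 where the pre-shift level gives +0.65, and one at 24 h gives 0.00 where the level gives +0.73. Acute responses near 6 h are read correctly (+0.75 with same-day exposure).

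The direction follows from b(c − 1) and the sampling times. The sizes rest on assumed response curves, effect, noise and sampling times, since the documents give no kinetics for any candidate marker. How many candidates respond in the affected range is therefore unknown, and the documents do not show that any particular marker would be lost. The consequence is a risk to aims 2 and 4: a delayed marker may be dropped or its sampling time set wrongly.

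**What to change.** State the outcome scale for each analysis in the Statistical Analysis section:

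- **Lagged exposure and biomarker selection:** model log pre-shift and log post-shift levels as repeated outcomes in one mixed model. Include a worker random intercept, a shift-time indicator (pre or post), and lagged exposure with its interaction with shift time. Handle values below the detection or quantification limit as censored, measurement by measurement. The interaction shows in which sample a response appears, which is what the sampling plan needs.
- **Same-shift effects:** keep the post-/pre-shift ratio, on the log scale, and say that it is used for these effects only.
- **Selection rule:** state that a marker's correlation with exposure is judged on the level models at the relevant lag, since the field study will have one level per worker.

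The change needs no new samples, and the model types are those that the plan already names. The cost is some re-analysis, because Project Temporality and Duration says that part of the pilot's statistical analysis has begun.

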### Research Setting and Participants

The research will be conducted in a Parisian urban transport company in France for the experimental part and at Unisanté in Switzerland for the analytical part. The study samples will comprise three categories of underground subway workers: locomotive operators, security guards, and station agents in charge of information, ticket sale and control. All these professionals have their workstations underground. These jobs are considered the most exposed to PM compared to other professionals working outdoor, such as bus or tram drivers, controllers and administrative staff. They are also less concerned with other chemical exposure compared to maintenance workers.

The pilot longitudinal study will use a convenience sample of nine workers; three workers per occupation. Both women and men aged 40+, and non-smokers for at least 10 years (to avoid interference of smoking with the exposure-biomarkers-health outcome relationships) will be considered eligible. The only exclusion criteria are a counter-indication of spirometry test and acute or chronic morbidities other than COPD. The participants will have their workstations on subway line 7. This line is entirely underground, deep, has no mechanical ventilation and therefore represents one of the worst case scenarios in terms of exposure and one of the best for setting a pilot study. It offers a possibility to set up rooms for participant reception, biological sampling and equipment storage. The workers recruitment will be managed by the medical coordinator of the study. The medical coordinator will organise internal company meetings with workers, their supervisors and occupational physicians. At these meetings, workers will be informed on the objectives of the pilot study, inclusion criteria and invited to contact their occupational physician to declare their wish to participate in the study and to arrange an individual interview for this purpose. The occupational physicians will check the inclusion and exclusion criteria and collect the signed written informed consent form eligible workers. The recruitment of workers will be carried out in chronological order: The eligible workers who volunteer first will be given priority.

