**Fig. 1 Fig1:**
[figure not shown]
Preparatory actions and measurements carried out every day for each participant during two-week prospective follow-up in the pilot study

In contrast to the pilot study, the field study will focus only on the biomarkers pre-selected in the pilot study as well as health outcomes, which will be measured only once per worker. All workers will be asked to fill in a standardized questionnaire, very similar to the questionnaire used in the pilot study. COPD diagnosis will be the principal clinical outcome. COPD assessment will be based on the 2017 update of the Global Initiative for Chronic Obstructive Lung Disease (GOLD) Guidelines [42]. Here, COPD is defined by incompletely reversible airways obstruction—that is, a ratio of the post-bronchodilator forced expiratory volume in 1 second to the forced vital capacity (FEV1/FVC ratio) of less than 70% in presence of the clinical symptoms such as dyspnea, chronic cough or sputum production. The GOLD guidelines recognize that the use of fixed FEV1/FVC ratio values will result in more frequent COPD diagnosis in elderly, and in less frequent diagnosis among adults younger than 45 years, especially for mild COPD. The lower limit of normal (LLN) values of FEV1/FVC, based on the normal distribution, classify the bottom 5% of healthy population as abnormal [42]. Considering the age-distribution within the cohort of the Parisian transport company workers [43], we will use the LLN values of FEV1/FVC as a second definition of COPD. For these LLN values, spirometric reference values determined from multi-ethnic reference values for spirometry for the 3–95-year age range (the global lung function 2012 equations) will be used [44]. The same well-trained occupational physician will perform spirometry to avoid inter-assessor differences. For every obstructive syndrome suspicion, a reversibility test by bronchodilation will be performed, to make a differential diagnosis between COPD and asthma. This and secondary health outcomes of interest are described in Table 2. The course of the typical medical check for the field study is depicted in Fig. 2. We will use the same methods for EBC, exhaled air and urine collection as those used in the pilot study and two single use cytobrushes (Cepilo cervical cell sampler, Deltalab S.L.U., Spain, cat. No. 440150) for harvesting buccal cells (< 5 minutes) (Table 3).

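### The pilot's rule for choosing field biomarkers has no term for within-worker reliability, although the field study classifies a chronic disease from one measurement per worker; a coarse reliability screen would be a cheap improvement

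*Protocol article*

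**What the plan says.** Under Statistical Analysis, the protocol article gives the rule that carries markers from the pilot to the field study: "The most informative biomarkers (i.e., correlated both with exposure and particularly with FEV1/FVC ratio) will be selected for the field study". The same paragraph fixes the scale of the correlations (external with internal exposure, internal exposure with effect markers, effect markers with FEV1/FVC): "using post-shift to pre-shift values ratios for each biomarker". It also plans the models for the repeats: "Repeated data will be analyzed using mixed linear models and interval regression models for the censured data (below LOD/LOQ".

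The pilot is small but dense. Under Research Setting and Participants: "The pilot longitudinal study will use a convenience sample of nine workers". The Discussion counts "twenty measurements per participant for urine and EBC", which matches sampling before and after the shift over two working weeks.

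For the field study, Exposure and Health Outcome Measures says that it covers the pre-selected biomarkers and "health outcomes, which will be measured only once per worker". The grammar could tie the single measurement to the health outcomes alone. However, Project Temporality and Duration describes one medical check of at most two hours per participant, so one biomarker sampling per worker is the natural reading.

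The Discussion itself says that the pilot relations are short-term, whereas COPD is chronic.

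**The concern.** A marker measured once can separate COPD cases from controls only as far as that one value reflects the worker's usual level. What governs this is the ratio of between-worker variance to total variance, the ICC. The rule has no such term.

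The chosen scale adds to the problem. If a log marker is the worker's stable level plus a shift effect plus noise, the post/pre ratio is a difference of logs and the stable level drops out. Both correlations are then largely correlations with shift response. A marker whose usual level tracks lung function, but which does not move over a shift, has little chance of being picked.

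At stake is the field study's central hypothesis, that a panel including OPEA diagnoses COPD better than a single marker. If the markers added to OPEA are unstable within a worker, a panel that shows no gain would be hard to interpret. It could mean no biological information, or a choice of markers that a single sample cannot exploit.

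**Working it through.** **Inputs from the article.** Nine pilot workers; 20 urine and EBC samples each, so 20/2 = 10 pre-shift samples each; one field measurement per worker; correlations on post/pre ratios. The article gives no ICC and no AUC for any marker other than OPEA, so there is no planned figure to reproduce on this point. The ICC values below are assumptions, and 0.70 is used only as a round starting AUC.

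**1. What one sample costs.** Under a binormal model, single-sample AUC = Φ(√ICC × Φ⁻¹(person-level AUC)). Φ⁻¹(0.70) = 0.5244.

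| ICC | √ICC | √ICC × 0.5244 | single-sample AUC |
|---|---|---|---|
| 0.8 | 0.894 | 0.469 | 0.680 |
| 0.5 | 0.707 | 0.371 | 0.645 |
| 0.3 | 0.548 | 0.287 | 0.613 |

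**2. What the ratio scale removes.** Take a marker whose stable level correlates −0.8 with FEV1/FVC and which has no shift response. Simulated with nine workers and ten days, its mean correlation with FEV1/FVC is about 0.00 on the post/pre scale and about −0.74 on pre-shift levels. The stated scale would miss it.

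**3. Does the rule pick unreliable markers?** An illustrative simulation used 20 candidate markers, nine workers and ten days. Single-measure reliabilities were assumed to lie between about 0.09 and 0.83, and five markers were chosen. The stated rule was represented by giving its two correlations equal weight.

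| Selection | mean reliability | single-sample AUC from 0.70 |
|---|---|---|
| none | 0.46 | 0.639 |
| exposure correlation alone | 0.40 | 0.629 |
| stated rule | 0.42 | 0.633 |
| pilot ICC | 0.69 | 0.668 |

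Against no selection, the stated rule loses 0.639 − 0.633 = 0.006. Against selection by ICC, it forgoes 0.668 − 0.633 = 0.035. A second simulation under other assumptions gave 0.56 for the stated rule against 0.53 for no selection, rising to 0.64 when an ICC screen was added. The rule is thus roughly neutral for reliability; what it lacks is a screen.

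**4. What nine workers can estimate.** One-way ANOVA with 9 workers × 10 samples, estimated ICC 0.5: F = (1 + 9 × 0.5)/(1 − 0.5) = 11. The 97.5% and 2.5% points of F(8, 81) are 2.353 and 0.266. The limits for F are 11/2.353 = 4.68 and 11/0.266 = 41.3. With ICC = (F − 1)/(F + 9), the 95% interval is 0.27 to 0.80. By the same distribution, a hard cut at 0.5 would reject about 30% of markers with a true ICC of 0.6 and pass about 19% with a true ICC of 0.4.

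**The case against.** **Temporal variation is studied.** The pilot aims to set the sampling plan by half-life and plans lag-time analyses and mixed models. This stands as a description of the pilot. But that work bears on when to sample; nothing in the article feeds it into which marker is chosen, and the rule is worded as a definition.

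**The rule leans on FEV1/FVC, not on exposure alone.** This is true, and a reader might infer from the exposure criterion that the noisiest markers will be selected. The documents do not support that: simulated reliability under the stated rule is close to that of no selection. The weight on FEV1/FVC helps less than it seems, however, because that correlation too is computed on ratios.

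**The planned power is not touched.** A reader might apply the attenuation to the AUCs of 0.64 and 0.70 in the sample-size text and conclude that the field study loses power. That does not follow. Those AUCs are for OPEA, which is in the field hypothesis in advance, so the rule cannot affect it. They also rest on observed OPEA values from a preliminary study whose number of readings per person is not stated, so single-reading noise may already be in them.

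**A single reading is the intended use.** If the test is to be one quick measurement, its single-sample AUC is the right target, and a weak panel would be a valid result. This stands, but it is a reason to choose markers that perform well on one sample.

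**A condensed article may leave numeric criteria to the fuller protocol.** This is fair for a numeric floor, and no such omission is held against the plan. The point is the rule and scale that the article does state.

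**Exposure correlation serves a stated aim**, namely suitability for surveying exposed workers. This stands, and the criterion should stay.

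**Conclusion.** The point holds as a cheap improvement, not as an error that undermines the field study. The stated rule selects on short-term behaviour, on a scale that removes the stable between-worker level, for a one-measurement classification of a chronic disease. It makes no use of the reliability information that the pilot can supply. Markers that discriminate poorly on a single sample may therefore enter, and the non-OPEA part of the panel may be weaker than it need be.

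The size cannot be determined from the article. That the field AUC will in fact be attenuated by a given amount is something a reader might infer, but it depends wholly on an assumed ICC. The table in step 1 shows a range from slight to substantial. It rests on a binormal model and a hypothetical person-level AUC of 0.70 for a non-OPEA marker.

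**What to change.** In the selection rule under Statistical Analysis:

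- For each candidate COPD-panel marker, report the ICC on pre-shift values with its interval, from the mixed models already planned, and the share of samples above LOQ.
- State in advance that these act as a coarse screen alongside the two correlations. Drop only markers that are clearly unreliable, with no fine ranking and no hard cut at 0.5.
- Judge the association with FEV1/FVC on pre-shift levels as well as on post/pre ratios.
- Keep the correlation with exposure for the surveillance aim, but do not let it alone exclude a diagnostic candidate.

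The cost is a change of wording and some added output; no new samples or models are needed. The downside is imprecision, as step 4 shows. The pilot workers are also more alike than the field population: aged 40 or over, non-smokers for at least ten years, without other morbidity and on one line, whereas the field study takes adults of any smoking status. The pilot may therefore understate between-worker variance, and hence the ICC in the field, which is a further reason to keep the screen lenient.
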